### Participants

The participants will be HNC patients of the Brazilian public health system—Brazilian Unified Health System (Sistema Único de Saúde (SUS))—who will be treated with RT, with or without CT, in Araujo Jorge Hospital, Goiânia, Goiás, Brazil. To estimate the study sample size, we used the OpenEpi online calculator (http://www.openepi.com). The 95% significance level (1 – α error type I), a study power of 80% (1 – β error type II) and a 1.0 ratio of unexposed/exposed were set as estimator parameters. Finally, we considered a prevalence of severe OM of 60% for the control group and 21% for the PBMT group (OR = 0.18) [18]. The calculated minimum sample size was 50 participants (25 per group) and an additional 10% was considered to compensate for possible loss to follow-up.

Individuals older than 18 years of age of both sexes will be included in the study, edentulous or not, with neoplastic lesions in the head and neck site (oral cavity, oropharynx, nasopharynx and advanced stage laryngeal tumors; T3 N1 or T3 N2 and T4 with any N status). All participants will be subjected to RT (with or without CT), with a minimum dose of 50 Gy, 2 Gy/day and five times per week, in the conventional scheme of RT. All patients will be treated with the Elekta Compact (Elekta AB, Stockholm, Sweden), a linear accelerator that generates photon radiation with fixed energy of 6 MV. Participants will be excluded if they present with an infection or salivary gland tumors, Sjögren’s syndrome, are submitted to palliative treatment or were previously treated with RT and/or CT in the head and neck area. Individuals diagnosed with lymphoma, melanoma or skin cancer will also be excluded.

In this hospital setting, every HNC patient who will be submitted to RT must be evaluated by the Dental Care Service to obtain authorization before starting the HNC treatment. On this occasion, the individuals will be invited to participate in the study. After acceptance, the principle researcher will obtain a signed written informed consent form from the participants. Participants will be excluded from the trial in cases of death, withdrawal or absence from five or more laser therapy sessions.

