### Statistical analysis of data

The comparison of the clinical and demographic characteristics of the participants between the two groups will be performed using the Pearson chi-square test for categorical variables. The Mann–Whitney test will be used to compare the severity of OM and concentration of cytokines between the two groups. The Friedman test will be used to compare changes in outcomes in the different time points for each of the treatment groups. In case of nonrejection of the null hypothesis, a post-hoc power analysis will be performed to test whether the study has sufficient power to identify the differences between groups. Values of *p* < 0.05 will be considered statistically significant. The statistical analysis will be performed using the IBM SPSS 20.0 statistical package (SPSS Inc., Chicago, IL, USA).

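### Non-significant results trigger a post-hoc power analysis with no stated target effect, which cannot show what differences the data rule out

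*Protocol article*

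**What the plan says.** The Protocol article, section Statistical analysis of data, assigns the between-group analysis in one line: the Mann–Whitney "test will be used to compare the severity of OM and concentration of cytokines between the two groups". The threshold is p "< 0.05 will be considered statistically significant". It then says how a null result is followed up: "In case of nonrejection of the null hypothesis, a post-hoc power analysis will be performed to test whether the study has sufficient power". What that power is meant to detect is described only by the phrase "to identify the differences between groups".

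That is the only guidance the section gives for a null result. It names no target difference for the power calculation and does not refer back to the sample-size paragraph.

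That paragraph, in the Participants section, uses "The 95% significance level" (evidently alpha = 0.05), 80% power, 1:1 allocation and "a prevalence of severe OM of 60% for the control group and 21% for the PBMT group". It arrives at 25 per group, with a further 10% for losses. No design effect is given for cytokines, OHIP-14 or PROMS.

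**The concern.** A reader facing a non-significant result needs to know which differences the data still allow and which they exclude. A power figure computed after the result answers neither question. At the observed difference it carries essentially the same information as the p-value. At the planned difference it carries no information from the data beyond the number analysed.

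Because the sentence does not say which is meant, the analyst may choose once the result is known, and for severe OM the two choices point in opposite directions. The calculation is also triggered only by non-rejection, so null findings get an extra gloss that significant ones do not. The article says its results are meant to inform public policy-makers on adopting photobiomodulation therapy (PBMT), so it matters that a null result can be read fairly.

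**Working it through.** **Inputs.** From Statistical analysis of data: threshold 0.05 (two-sided assumed, as sidedness is not stated) and the Mann–Whitney test. From Participants: 60% versus 21%, 80% power, 25 per group, plus 10%. The last gives 50 × 1.1 = 55, or 50/0.9 = 55.6, so 28 per arm after rounding up.

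**1. The plan's own figure.** With mean proportion (0.60 + 0.21)/2 = 0.405 and difference 0.39:

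n = 2 × 0.405 × 0.595 × (1.960 + 0.842)² / 0.39² = 24.87, so 25 per arm and 50 in total. The stated sample size is reproduced and is not in dispute.

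**2. Power at the observed difference.** For an approximately normal statistic, let z_p = Φ⁻¹(1 − p/2). Then

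observed power = Φ(z_p − 1.96) + Φ(−z_p − 1.96).

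| p | Observed power |
|---|---|
| 0.05 | 50.0% |
| 0.06 | 46.9% |
| 0.10 | 37.6% |
| 0.20 | 24.9% |
| 0.50 | 10.4% |
| 0.80 | 5.7% |

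Only p enters the formula. Since z_p < 1.96 whenever p > 0.05, the result cannot exceed about 50%.

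**3. Does this hold for the kinds of test relevant here?**

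- *Chi-square on severe OM.* Power was computed at the observed rates for every non-degenerate 2×2 table with p ≥ 0.05. The maximum was 47.1% with 25 per arm (4/25 versus 10/25, p = 0.059) and 49.8% with 28 per arm.
- *Fisher's exact test.* With the p-value taken from Fisher and power from the same normal approximation, the maximum was 66.3% with 25 per arm (0/25 versus 5/25, p = 0.0502) and 65.7% with 28 per arm.
- *Mann–Whitney.* 300 lognormal data sets were simulated with 25 per arm, and power was obtained by resampling each one. All 205 non-significant sets fell below 80% (maximum 53%). The rank correlation between p-value and observed power was −0.995. This mimics cytokine-type data; ordinal OM grades with ties were not simulated.

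The 50% ceiling is therefore a feature of the normal approximation, but no case checked reached 80%.

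**4. Power at the design effect.** With 25 per arm:

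- null standard error = √(2 × 0.405 × 0.595/25) = 0.1388
- alternative standard error = √((0.60 × 0.40 + 0.21 × 0.79)/25) = 0.1274
- power = Φ((0.39 − 1.96 × 0.1388)/0.1274) = Φ(0.925) = 82.3%

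With 28 per arm it is 86.5%. Exact enumeration of the chi-square test gives 84.8% and 86.2%. These figures were available before enrolment.

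**5. The two readings on one hypothetical result.** Suppose severe OM occurs in 15/25 controls and 13/25 PBMT patients, an 8-point reduction.

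- Test: z = 0.08/√(2 × 0.56 × 0.44/25) = 0.57, p ≈ 0.57.
- Power at the observed difference: about 9%, which reads as underpowered.
- Power at the design effect: about 82%, which reads as adequately powered.
- Wald 95% confidence interval: 0.08 ± 1.96 × √((0.60 × 0.40 + 0.52 × 0.48)/25) = 0.08 ± 0.274, or about −19 to +35 points.

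Only the interval shows what the data leave open: anything from appreciable harm to a large benefit.

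**The case against.** The strongest reply is that the sentence does not say at which effect power will be computed. At the design effect a null severe-OM result would be called adequately powered, which is the opposite of a built-in excuse. This stands, and it limits the point: the underpowered label follows only on the observed-difference reading. That reading is still the more natural one. The calculation is triggered by the result, it refers to the differences between groups, and no design effect exists for the other outcomes.

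A reader might go further and infer that every null result will be reported as underpowered, so that the trial could never conclude against PBMT. The documents do not support this:

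- The sentence says that a calculation will be done, not how null results will be worded.
- The cost-effectiveness ratios under Cost-effectiveness analysis depend on neither a significance test nor post-hoc power, so PBMT could prove costlier with little benefit whatever the power figure.
- A significant result favouring control would not trigger the rule.
- The statistical section names no between-group test for quality of life, so extending the effect to OHIP-14 or PROMS is inference.
- A directional hypothesis is ordinary and is not evidence of a defect.

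It is also fair to object that the exact link between p and observed power is a normal-theory result. For the Mann–Whitney test the link was close but not perfect, and the 50% ceiling was slightly exceeded.

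**Conclusion.** The point holds in a limited form. The plan fixes a method for following up null results that cannot do the job on either reading. At the observed difference it adds essentially nothing to the p-value: about 50% or less under the normal approximation, at most 53% in the Mann–Whitney simulation and 66.3% with Fisher, never 80%. A null OM-severity or cytokine result would then look underpowered. At the design effect, for severe OM only, it returns about 82–86% regardless of the data. The sentence leaves the choice between these opposite answers until after the result.

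This rests on a two-sided 0.05 level and, for the first reading, on the assumption that power is computed at the observed effect. The severe-OM figures use a comparison of proportions, as the sample-size calculation does, although the statistical section names Mann–Whitney on severity. The sentence alters no estimate, p-value or cost-effectiveness ratio; the damage is to how a null result is interpreted. The sample size is not at fault.

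**What to change.** Delete the sentence on post-hoc power and replace it with something like:

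> Each between-group comparison, whether or not statistically significant, will be reported as an effect estimate with a 95% confidence interval: the difference in proportions for severe OM, and the Hodges–Lehmann shift for OM severity and cytokine concentrations. Non-significant results will be interpreted by the range of differences that the interval still allows, read against a smallest relevant difference specified before the analysis.

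The 39-point planning difference (60% − 21%) should not serve as that benchmark. In the example above, the interval of about −19 to +35 points excludes 39 yet remains compatible with a 35-point reduction, so excluding 39 would not show that a relevant benefit is absent.

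The cost is a few sentences, plus agreement on the smallest relevant differences before the analysis. No new data, participants or change to treatment are needed.

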## Discussion

This is the first cost-effectiveness study to include patient-reported outcomes to assess the effectiveness of PMBT in the treatment and prevention of severe OM in patients undergoing HNC treatment. The inclusion of patient-reported outcomes, such as oral health-related QoL, is important in cost-effectiveness studies because this allows comparisons between different technologies. Although PBMT is one of the most effective therapies for OM, other treatments have been studied; for example, the use of keratinocyte growth factor, date palm pollen, gamma-d-glutamyl-l-tryptophan, pilocarpine hydrochloride, superoxide dismutase mimetic and ATL-104 mouthwash [42–51]. In a recent literature review, Cinausero et al. [51] discussed several strategies to treat and manage OM, ranging from basic oral hygiene to physical strategies, including PBMT and natural medicines. Since several treatments are available for OM management, patient-reported outcomes, like the ones that will be evaluated in this study, allow for comparisons between the cost-effectiveness of different treatments suggested for OM. Besides that, the investigation of inflammatory cytokines and oxidative stress in the saliva of the participants will contribute to the elucidation of the mechanism of action in OM associated with chemoradiation.

Shariati et al. [52] pointed out that the lack of attention to the field of dentistry from public policy-makers discourages economic studies, and effective and beneficial health services are neglected because of this. This study aims to consolidate the use of PBMT to treat and prevent severe OM, mainly in the public health system, which currently does not provide any treatment for this condition but only for the pain associated with it. Adequate resource allocation and cost reduction are expected from the results of this study, as well as an improvement in the QoL of the HNC patients.

Cost-effectiveness studies about OM treatment are rare [29, 53]. Antunes et al. [29] found that the ICER was US$4961.37 per severe OM case prevented, also considering the SUS. However, the authors did not investigate any patient-reported outcomes, such as QoL, as we propose in this study. Elad and Thierer [53] studied the cost-effectiveness of topical chlorhexidine in decreasing the risk of mortality, and OM was an important outcome evaluated. The authors found that chlorhexidine mouthwash was more effective and less costly than not using it. However, the expected outcomes were analyzed throughout a static model using secondary data that had been previously published, carried out considering hematologic patients.

Currently, several PBMT protocols are considered when treating OM [18]. The energy per spot and the laser schedule are the most important parameters that differ among the studies. The red laser is most frequently used and presents favorable results. In our study, a diode laser will be used with a wavelength of 660 nm (red laser), 25 mW of power and 0.24 J of energy per point. The PBMT will be performed daily until the end of the HNC treatment. This protocol was used by Oton-Leite et al. [30] and satisfactory results were achieved.

In a recent study, Sonis et al. [54] discussed the effect of PBMT on tumor growth, proliferation, local invasion, metastases and the treatment response of the tumor. Based on the results of the studies that suggested upregulation and downregulation of genes and pathways associated with these aspects, and the lack of strong evidence regarding the safety of use of PBMT, the authors discouraged the use of PBMT as a treatment for OM. However, to date, the Multinational Association of Supportive Care in Cancer and the International Society of Oral Oncology still consider and recommend PBMT as an intervention for OM [55]. Use of PBMT is also associated with a lower frequency of interruption of the oncological therapy, and this may play an important role in the prognosis and chance of cure for the patient [24]. Corroborating these studies, Antunes et al. [56] showed that HNC patients who were submitted to PBMT presented a tendency of better overall and disease-free survival when compared with patients submitted to placebo. Additionally, the progression-free survival was significantly higher among patients submitted to PBMT and a better response to HNC treatment was observed. We believe it is important to study the effects of PBMT on inflammatory mediators and oxidative stress, so that a safety protocol and guideline can be established and proposed. Additionally, the diversity of PBMT protocols reported in the literature make it difficult to discuss the results from the different studies.

Finally, the effectiveness of PBMT is well established in the literature. This investigation aims to establish a safety evidence-based protocol for the use of PBMT in the treatment and prevention of severe OM, mainly in the public health system. The results of the investigation will be important to public policy-makers since they may enhance understanding regarding the costs involved in OM treatment and prevention with PBMT, favoring better resource allocation. Additionally, the investigation is also important to HNC patients since the results will encourage the incorporation of PBMT into the public health system, resulting in a better QoL for the patients during treatment.

## Trial status

The trial started recruitment and treatment of participants in August 2017.

## Abbreviations

CRT: Chemoradiation therapy
CT: Chemotherapy
EAC: Equivalent annual cost
HNC: Head and neck cancer
ICER: Incremental cost-effectiveness ratio
*n*: Discount index
NCI: National Cancer Institute
OHIP-14: Oral Health Impact Profile-14
OM: Oral mucositis
PBMT: Photobiomodulation therapy
PROMS: Patient-Reported Oral Mucositis Symptoms
QoL: Quality of life
RT: Radiotherapy
SUS: Brazilian Public Health System
*t*: Useful life
WHO: World Health Organization
*x*: Purchase price
